**Please see Appendix 3 for the types of physiological tests that will be done and where they will be done.**

**Study 2**

***Pilot pharmacokinetic, pharmacodynamic and safety study of exogenous arginine in uncomplicated falciparum malaria:***

*Overview:* In this pilot study in uncomplicated malaria we will generate initial safety, pharmacokinetic and pharmacodynamic data for exogenous arginine administration. We will use a dose-escalation design; all doses (3-12g) will be in the low-mid range of dosages previously used safely in humans (6-30g). *Dosing:* All doses of arginine hydrochloride will be infused intravenously over 30 mins (which is the standard infusion time). Initial dosing will be 3g (n=10), increasing to 6g (n=10), increasing to 12g (n=10) if lack of significant toxicity is demonstrated at each dosing level. Each arginine dose will be added to 100ml normal saline (the standard diluent safely used in other studies) such that total concentration is ≤10% (see CRF)

In addition to arginine, all subjects will be treated with standard antimalarial drugs (currently quinine) as per standard RSMM/Depkes practice/protocols.

*Clinical measures.* Vital signs (pulse rate, BP, temperature, respiration rate), and a standardised clinical assessment (symptom/sign list) will be serially monitored over 48 hours (see table 2). ECG will be monitored from -60 to 240 mins.

*Blood sampling*:

Two venous cannulae will be placed:

A cannula in the right forearm will be used for administration of IV arginine, and for any IV fluids required after arginine administration.

A cannula in the left forearm or antecubital fossa for sampling of venous blood, placed one hour prior to arginine adminstration.

At the time of cannula insertion we will take 7 ml heparinised baseline blood. This will be the -60 minute sample: 60ul will be used for baseline iSTAT EC8+ measurement of electrolytes, glucose, urea, and bicarbonate. The remainder will be processed as per NO Study II SOP for heparinised blood.

Subsequent sampling regimen (from cannula): up to 18 ml (in heparin) over the next 20 hours, taken in up to 9 divided aliquots during this time interval. *Including the enrolment sample, this amounts to a maximum of 25ml taken over 21 hours.* For study 2, we will use a sampling protocol as outlined in table 2, with frequent initial samplings in an approximate geometric time series to include at least four half lives of arginine, plus one blood sample the following morning. These samples include serial measurements required for clinical management of malaria (including serial parasitemia, blood glucose), pharmacokinetics of arginine (arginine, its metabolites, and related amino acids), pharmacodynamic measures (NO metabolites and oxidant production, electrolytes, pH) and biomarkers of response to antimalarial treatment (including lactate, glucose and parasitemia [see example table 2]); and safety, including serial glucose, K+, Cl-, HCO3-, pH, PO43-, and a final measurement at 20 hours for urea, creatinine, lactate, liver enzymes and creatine kinase.

We will also measure exhaled NO online at each of these time points, using ATS Guidelines44.

Please see attached ATS guidelines behind the protocol.

*Additional Physiological assessments:*

*Vascular studies:* As additional pharmacodynamic measures, we will also use serial non-invasive vascular sonography to assess effects on endothelial function by brachial dilatation, microvascular blood flow by Doppler assessment of peak reactive blood flow and finger plethysmography (see Study 1).

*Gas Transfer* (DLCO) and *physiological deadspace*: to examine effects on organ-specific function we will use our existing pulmonary physiology apparatus and procedures at RSMM (HREC 02/13) to measure gas transfer and pulmonary deadspace at intervals outlined in table 2.

*Interpretation:* Pharmacokinetic models will be fitted to concentration-time and concentration-effect data from studies (a) and (c) using NONMEM (v. 5)51, to provide population parameter estimates, mean parameter values and their between-subject variability where possible. This analysis will include assessment of possible covariate relationships, where parameter values such as clearance may be correlated with patient demographics such as age. A model will be developed that describes the time course of effects of arginine in terms of NO production (plasma NOx/creatinine ratio [systemic NO production] and exhaled NO [pulmonary NO production]), oxidant stress, endothelial function, microvascular flow and gas transfer/physiological deadspace. It is also intended to address biomarkers of effectiveness. **[name] from NIHRD will be invited to the Dept Pharmacy in Brisbane to join the NONMEM modeling for the PK-PD relationships outlined above.**

Safety data from study 2 will be reviewed by an experienced independent data monitoring committee (see appendix) before proceeding to study 3. The pharmacokinetic-pharmacodynamic model developed in study 2 will enable us to predict the dosing and best sampling schedule (both pharmacokinetic and pharmacodynamic) for use in study 3. If the pharmacokinetic-pharmacodynamic model suggests that a higher dose than 12g may be required, a dose of up to 18 g may tested in stage 2 of the study prior to commencing stage 3.

*Potential adverse effects (in study 2 and study 3) and study response:* A number of adverse effects have been previously noted with large *supraphysiological* dosing in subjects with normal plasma arginine levels. These have been infrequent and usually at the standard high dose (≥30g) required to stimulate growth hormone release, **a *dose that will not be used in our studies.*** Arginine is a natural product that has been widely used in subjects with cardiovascular disease, sickle cell disease, and sepsis, with an excellent safety profile. This study primarily examines pharmacokinetic-pharmacodynamic modeling, but will also confirm safety in uncomplicated malaria.

**Patients with uncomplicated malaria in Indonesia have mean levels of arginine *below* normal, and combined with a dose well below the standard 30g IV dose used in other settings, we do not expect significant adverse effects to occur. Whilst we believe the following adverse effects to be very unlikely, our protocol allows us to detect, and if necessary rectify them:**

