
*Clinical use of arginine in humans:*L-arginine has been safely used in humans for decades16,32. Arginine has also been well tolerated when given short term (6-30g IV/orally) and long term (6-12 g/day orally) in healthy subjects, and subjects with severe cardiovascular disease and cystic fibrosis with minimal toxicity16,17,32-35. In these diseases, arginine increases NO metabolites and exhaled NO, with improvements in endothelial function, perfusion, symptom scores and exercise tolerance16,17,33,34. Use of 12g IV arginine in sepsis has been shown to improve cardiac output and improve oxygen transport35a. L-arginine therapy corrects the hypoargininemia and impaired NO production found in patients with sickle cell vaso-occlusive syndrome (SCD VOCS),12 a syndrome with endothelial dysfunction and impaired NO production similar to malaria11. Pharmacokinetic data have not been reported in SCD12,36. A randomised trial of L-arginine in SCD VOCS is in progress with no significant adverse effects using 0.1 g/kg IV 8 hrly ([name], personal communication, 2004). Use of enteral arginine supplementation (with or without other “immunonutritional” supplements) in critically unwell intensive care unit patients has been associated with reduced inotrope requirements, higher base excess, reduced risk of nosocomial infection, reduced ventilator days and reduced hospital stay,37-40,41. Beneifts were particularly noteworthy in septic ICU patients41. Use of oral arginine in patients with tuberculosis showed an increase in weight gain, reduced sputum conversion time and reduced symptoms compared to controls41a. Arginine is off-patent and available as an inexpensive, generic, GMP-standard product for human use. For potential adverse effects of arginine (in a malaria context) see “Study 2” below.

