**3. Rationale for the Arginine-NO studies:**

There is a need for novel adjunctive antidisease therapies to reduce the unacceptably high case-fatality of severe malaria (SM) further1,2. Irrespective of its cause, hypoargininemia likely limits NO production and is associated with death in cerebral malaria25. Our NO-arginine-malaria studies and the results of arginine trials in related diseases suggest that arginine may have potential for therapeutic use in malaria. L-arginine is commercially available as an off-patent product for human use, is inexpensive, and has been widely used worldwide with little toxicity despite supra-physiological intravenous dosing as a diagnostic pituitary function test and administration in other human diseases36 (see also “clinical use of arginine in humans” above). It is important to determine whether arginine administered to malaria patients increases NO production, reduces measures of oxidant stress and has physiological effects at the doses proposed: this has implications for understanding the pathophysiology of severe malaria, as well as therapeutic implications. Arginine pharmacokinetics have not yet been described in hypoargininemic states such as uncomplicated and severe malaria. Our proposed safety, pharmacokinetic-pharmacodynamic and efficacy studies in uncomplicated malaria will be the first steps in cautiously determining if exogenous arginine administration has therapeutic potential in malaria.

**4. Our aims** are to:

4.1 Determine the natural history of recovery of plasma arginine levels and our pharmacodynamic measurements in uncomplicated and severe malaria.

4.2 Determine the pharmacokinetics, pharmacodynamics and safety of L-arginine in uncomplicated malaria**.**

4.3 Determine preliminary effects on biomarkers of outcome in uncomplicated malaria.

4.4 Establish the relationship between malaria disease severity and those measures used to monitor pharmacodynamic effects: exhaled NO, plasma/urine NO metabolites, oxidant stress, brachial artery dilatation, doppler evaluation of microvascular blood flow, physiological deadspace.

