**Study 3:**

***Randomised concentration controlled trial, safety, and pharmacokinetic study in uncomplicated malaria:***The pharmacokinetic-pharmacodynamic model [from studies 1 and 2)] will be used to determine an appropriate loading and maintenance dose of arginine in uncomplicated malaria, to achieve average plasma arginine concentrations of ~600 uM (a plasma level ~4 times the Km of CAT2 transporters for cellular uptake of extracellular arginine). *Prior to the commencement of study 3, the Data Monitoring Committee will review the dosing and sampling schedule we will calculate from the pharmacokinetic-pharmacodynamic model generated in studies 1-2.* In addition, the target concentration (600 mcM) may need to be readjusted based on the results from studies 1 and 2.

*Design:* Randomised Concentration Controlled Trial.

*Treatment allocation:* Patients with uncomplicated malaria will be randomized to receive one of two treatments:

i) Standard RSMM antimalarial drug regimen for falciparum malaria (currently quinine) plus normal saline placebo (loading dose of 100 ml over 30 mins plus maintenance infusion using same volume in [ii] below).

ii) Standard RSMM antimalarial drug regimen for falciparum malaria (currently quinine) plus IV arginine: loading dose as 30 min infusion (see CRF) followed by maintenance infusion over 12 hours. The doses of arginine will be determined from the pharmacokinetic-pharmacodynamic model to maintain a plasma level of 600uM.

An independent statistician will use computer-generated randomization to generate blocks of patient numbers for each treatment.

*Sample size:* Extrapolating from similar concentration controlled trials, we estimate approximately 20 subjects in each of the two groups. Sample size calculation will require the results of the natural history of arginine/NO/NOx levels during malaria (study 1), and the maximal improvement and time course of improvement following administration (study 2). Therefore the final sample size will be calculated based on the results of studies 1 and 2. The sample size will be reviewed by the Data Safety and Monitoring Committee, and each of the relevant ethics Committees will be notified prior to commencement of Study 3 with confirmation of the number of patients.

*Patient numbering and randomization*:

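### Stage 2 allows up to 18 g, above its 3-12 g range, on a model result alone, and no scheduled committee review of the 3-12 g safety data has to come first

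*Combined protocol and SAP*

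**What the plan says.** The Study 2 overview gives the range: "all doses (3-12g) will be in the low-mid range of dosages previously used safely in humans (6-30g"). Ten patients are planned at each of 3, 6 and 12 g, with escalation "if lack of significant toxicity is demonstrated at each dosing level". The stage 2 paragraph of the Summary also stops at 12 g.

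The Study 2 Interpretation paragraph then goes further: "If the pharmacokinetic-pharmacodynamic model suggests that a higher dose than 12g may be required, a dose of up to 18 g may tested". The same sentence places this step "in stage 2 of the study prior to commencing stage 3".

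Two committee reviews are scheduled:
- Study 2, Interpretation: "Safety data from study 2 will be reviewed by an experienced independent data monitoring committee (see appendix) before proceeding to study 3".
- Study 3, opening paragraph, before that study starts: "the Data Monitoring Committee will review the dosing and sampling schedule we will calculate" from the model.

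The adverse-effects text for Studies 2 and 3 sets limits at which an individual infusion stops. Under the heading on serious adverse events, it also lists five kinds of event that go immediately to the Chief Investigators and the committee Chair.

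**The concern.** What opens the step above 12 g is a finding about exposure and effect, not about safety. The protocol asks for committee review of model-derived dosing before Study 3, but does not ask for it before a model-derived dose above the planned range in Study 2.

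The protocol gives its own reasons for care. It states: "Arginine pharmacokinetics have not yet been described in hypoargininemic states such as uncomplicated and severe malaria". Its background section reports apparently non-linear kinetics, with a dose-dependent half-life, in adults with normal arginine levels, so results at 12 g need not scale in proportion. The intravenous dose that it cites in an acute infection is also 12 g: "Use of 12g IV arginine in sepsis has been shown to improve cardiac output".

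At stake is whether a pattern of moderate disturbances at 3-12 g would be seen by independent eyes before a higher dose is given to patients with uncomplicated malaria.

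**Working it through.** The plan gives no calculation for this step, so there is no figure to reproduce. The check is mainly one of sequence and coverage.

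**1. Sequence.** The higher dose is placed in stage 2, before stage 3. The safety review must precede Study 3, and so must the dosing review. All three items share one deadline, and nothing orders the reviews ahead of the 18 g dose.

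**2. What reaches the committee meanwhile.** Stop limits compared with the serious-event list:

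| Measure | Infusion stops | Immediate notice to Chair |
|---|---|---|
| Systolic BP | fall >25 mmHg, or <80 | only if <80 and unresponsive to saline |
| K+ | ≥6.0 meq/L on repeat, or significant ECG changes | only if >6.0 with ECG changes |
| Glucose | <4 mmol/L | not listed |
| Bicarbonate | <15 mmol/L | not listed |
| Anaphylaxis | yes | yes |

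Death, and a clinical need for high care, dialysis or ventilation, are also notified. Several patients at 12 g could therefore meet a stop limit for glucose, bicarbonate, a BP fall, or K+ without ECG changes, and none of these need reach the committee before 18 g is given.

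**3. Can the stop limits act in time?** All doses run from 0 to 30 minutes (dosing paragraph and table footnote). In Table 2 the first iSTAT after the start is at 30 minutes. The section on K+ puts its peak at 60-90 minutes after the start. On schedule, then, the full dose is in before K+, glucose or bicarbonate is rechecked. BP and ECG are followed during the infusion. For the biochemical limits, the decision to give the dose is the main control.

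**4. Size of the step and of the evidence.**
- 18/12 = 1.5 times the top planned dose; 18/30 = 0.60 of the 30 g diagnostic dose.
- One-sided 95% upper bound on an event rate when 0 of n have it: 1 − 0.05^(1/n).
 - n = 10 (12 g only): 1 − 0.05^(1/10) = 0.259.
 - n = 30 (all levels, assuming the same risk at each): 1 − 0.05^(1/30) = 0.095.

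Counts alone say little at these sizes, so the individual values matter.

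**5. Do the protocol's data predict harm at 18 g?** For K+, the largest rise cited at 30 g in normal subjects is 1.7 meq/L, and patients with baseline K+ of 4.2 or more are excluded. The result is below 4.2 + 1.7 = 5.9, under the 6.0 limit. If the rise scales linearly with dose (an assumption), it is 1.7 × 0.60 = 1.02 at 18 g, giving about 5.2. The acid load is 18 × 4.75 = 85.5 mEq, against 12 × 4.75 = 57 mEq at 12 g. The protocol cites a study with no pH change at 30 g, even in renal failure. None of this predicts that a limit will be reached.

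**The case against.** A reader might infer more than the text supports, and the case on the other side is substantial.

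- **That nobody independent would have looked at 3-12 g.** This goes too far. Listed serious events go to the committee Chair for immediate review throughout those cohorts. What is missing is a scheduled aggregate review.
- **That no toxicity condition applies to 18 g.** The higher dose is a further step in a dose-escalation study, and the condition "if lack of significant toxicity is demonstrated at each dosing level" plausibly carries over. The sentence names only the levels up to 12 g, but this is a matter of wording. The unstated cohort size is likewise missing detail, not a design fault.
- **That 18 g is dangerous.** The protocol cites prior use at 6-30 g. It also cites a renal study giving 500 mg/kg (35 g for a 70 kg adult) over 30 minutes, with improved renal blood flow and filtration. Individual stop limits and bedside monitoring apply at every dose.
- **That the protocol certainly has no gate.** The committee appendix it refers to is not in the supplied text; Appendices 1-5 cover other matters. A gate there cannot be excluded.
- **That review will in practice come second.** The timeline puts modelling and committee review in the same April-August 2005 entry. Dosing ahead of review is permitted, not planned. The ethics committees also review Studies 1-3, including the 18 g ceiling.
- **Why this step and not the doublings from 3 to 6 and 6 to 12 g?** This is a fair challenge. The 25.9% bound applies equally after 10 patients at any level and does not single out 18 g. The difference is that 18 g lies outside the stated range, rests on a model trigger, and falls when the committee is due to see these data anyway.

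These arguments limit the weight of the point. They do not supply the missing order between review and dose.

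**Conclusion.** The point stands as a cheap improvement to the conduct of the escalation. As written, up to 18 g, 1.5 times the top planned dose, may be given on a model result before any scheduled aggregate review of the 3-12 g safety data. Immediate notice of serious events narrows the gap without closing it, because glucose below 4, bicarbonate below 15, a systolic fall above 25 mmHg, and K+ at or above 6.0 without ECG changes are not on the list.

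The documents do not support a claim that 18 g is unsafe or that patients go unmonitored. The conclusion rests on the supplied text. If the committee appendix already contains the gate, a cross-reference in the Interpretation paragraph settles the matter.

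**What to change.** In the Study 2 Interpretation paragraph, require the existing data monitoring committee to review the 3-12 g safety data and approve before any dose above 12 g. Give it the individual K+, glucose, bicarbonate, BP and ECG values, and the number of patients meeting each stop limit in the adverse-effects section. No change is needed at the 3, 6 and 12 g steps. Two optional clarifications are to state the cohort size (for example 10, as at the other levels) and to repeat the toxicity condition for this step.

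The cost is one review and a short pause, incurred only if more than 12 g is proposed. The review could overlap the April-August 2005 modelling window. The timeline shows no cohort above 12 g, but September-November 2005 leaves 3 months before Study 3 begins in December. Study 2 plans 30 patients in 5 months (December 2004 to April 2005), or 6 a month. At that pace, which is assumed to hold, 10 patients would take 10/6 = 1.7 months.

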**Possible Adverse Effects and Monitoring and Rescue Treatments Protocols:**

**1. Adverse Effects Documented With Evidence**

*a) Effects on blood pressure:* Most patients receiving arginine have no significant effect on blood pressure. Any effects on blood pressure are usually minimal, even with the 30g IV dose used clinically, much higher than we expect to use in this study16,17. Endothelial NOS expression in severe malaria24 makes it important we monitor this closely. Arginine supplementation in sepsis has not significantly exacerbated hypotension41 despite demonstrated tissue NOS expression in sepsis52. In previous studies, any effect on blood pressure has been minor and seen during the infusion, returning rapidly (within minutes) to normal as soon as the infusion is finished. As outlined in table 2, to monitor for hypotension, the subject’s vital signs including blood pressure will be taken every 10-15 minutes prior to infusion, every 5-10 minutes during the infusion and for 15 minutes after the end of the infusion, then 10-15 minutely for the rest of the first hour after the end of the infusion, and half hourly for the next two hours, then 2-4 hourly thereafter.

Response: If systolic blood pressure falls >25 mmHg or below 80mmHg or if the attending clinician is clinically concerned, the arginine infusion will be stopped and legs elevated. Previous studies using higher doses of arginine than we will use in this study have shown the BP rapidly returns to normal within minutes of stopping the arginine infusion, and this is expected to be all that is required. If SBP persists < 80 mmHg, 0.9% saline will be infused at a rate based on the treating clinician’s clinical judgement.

*b) Electrolyte abnormalities:*

- *Effect on K+:* Hyperkalemia may result from redistribution of K+ from intracellular fluid to extracellular fluid. In seven of eight normal Italian subjects receiving high dose arginine (30g IV), mean plasma K+ transiently increased by 1.23± 0.17 meq/L (range 0.6-1.7), peaking at 60-90 mins after start of a 30 min IV infusion54. These data excluded one subject who had a “virtually negligible” increase54. Clinically significant hyperkalemia has been reported with large supraphysiological doses in patients with renal failure (30g IV)55 and combined liver failure/renal impairment (again with very high dosing of 59-95g IV)56, in subjects taking spironolactone (an exclusion criterion in this study). Mean plasma K+ in 58 Indonesian subjects with uncomplicated malaria (in our initial NO studies in Jayapura) is at the low end of normal range (3.4 meql/L), with only 1 subject out of 58 having a K+> 4.0 [4.5 meq/L]. Subjects with renal failure or baseline K+≥4.2 meq/L will not be included in studies 2 and 3. Moreover lower doses will be used in both of our studies than the 30g dose used in published studies. Therefore a rise in K+ to ≥ 6.0 meq/L will be very unlikely.

Response: If serum K+ rises to ≥ 6.0 meq/L it will be immediately repeated using the bedside iSTAT to exclude hemolysis of sample. If K+ ≥ 6.0 meq/L or if significant ECG changes of hyperkalemia develop, the infusion will be stopped and subjects will be given 10ml of 10% calcium gluconate for membrane stabilization. This will be followed by continuous ECG monitoring and 10-15 minutely monitoring of K+: if thought necessary by the attending clinician, 10 U of regular insulin will be administered with 25g of IV glucose to induce K+ shift into cells.

- *Hypophosphatemia:*

A clinically insignificant transient fall in serum phosphate is noted with 30g infusions, with the maximum fall below baseline of 1.11 mg/100ml (or 33%), peaking 60 mins after commencement of a 30 min infusion54. In no cases did phosphate levels fall to potentially clinically significant levels (<1 mg/dL)54. We will nevertheless measure phosphate levels at baseline and at 60 mins.

Response: Moderate hypophosphatemia (1-2.5 mg/dL) is almost always asymptomatic and requires no therapy. Moreover, transient hypophosphatemia following arginine infusion *will not reflect any depletion of total body phosphate* that is required for very low levels of plasma phosphate to cause clinical manifestations. Low phosphate will therefore not be treated unless deemed essential by the treating clinician.

*c)* *Thrombophlebitis* is very unusual, but has been described57. This is minimized by using ≤10% solutions. One episode of *an extravasation reaction* has been described in a child. This will be minimized by administering arginine as a 10% solution, and careful insertion and observation of IV canula/symptoms/signs during infusion.

Response: If extravasation occurs, the infusion will be stopped, the affected extremity elevated. The catheter/needle will not be removed immediately, but rather left in place to aspirate fluid from the extravasated. The line will then be removed and an ice pack applied.

*d)* *Anaphylaxis*: We are aware of only one report of a case of *anaphylaxis58*. This would seem a very rare event with an exogenous/endogenous amino acid and is considered extremely unlikely in current studies

Response: The arginine infusion will be ceased. Adrenaline and rescucitation facilities will be readily available in the high care unit at RSMM, to which the clinical research ward is attached. Standard treatment for anaphylaxis will be undertaken in the very unlikely event it would be required.

*e)* *Rash:* maculopapular rash: rare; causality not proven. Response: infusion will be stopped

*f) Minor adverse effects:* Arginine can uncommonly cause nausea, vomiting, flushing, headache, and numbness. These will be documented in the CRF. These are also common in malaria, and will not result in cessation of the infusion, unless patient requests to withdraw from the study. In previous studies with oral arginine in SCD, gastrointestinal symptoms (including abdominal cramping and diarrhea) were occasionally seen ([name], personal communication 2004), one of the reasons why they are now using IV arginine for the ongoing trial in SCD. Gastrointestinal side-effects (eg nausea, vomiting) have not been seen with IV infusion in SCD. Minor flushing has been seen.

